### Sample size considerations

Sample size calculations for this study are based on the 100 mm visual analogue scale for usual pain over the past week. The mean difference between baseline and final score for each group will be compared to measure the effectiveness of each intervention. In order to detect a minimal clinically important difference of 15 mm [15,27], assuming a standard deviation of 20 mm [10], a power of 0.80 and alpha level of 0.01, a sample size of 40 participants per group will be required. To account for dropouts, particularly considering the long duration of the study [28], a group size of 44 will be recruited, with a total sample size of 176.

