### Planned statistical analysis

Statistical analysis will be conducted on a blinded, intention to treat basis, with all participants who were initially randomised into the study included where data is available for each measurement time. SPSS software (Version 15.0) will be used for statistical procedures. The four groups will be examined for baseline comparability with respect to demographic data such as age, gender, body mass index and duration of knee pain, as well as baseline values of outcome measures. Continuous outcome measures taken at 6, 12 and 52 weeks will be analysed using univariate analysis of variance, where the baseline value of the outcome measure will be used as a covariate and group allocation as a fixed factor. Continuous data will also be expressed as area under the curve in order to compare the overall effectiveness of each intervention over the entire 12 month period. Participant demographics will also be included in the models as covariates to assess their impact on outcome. The dichotomous measure of success will be analysed using relative risk, risk reduction and numbers needed to treat in order to facilitate clinical interpretation of findings and future guidelines. Cost effectiveness analysis will evaluate the effectiveness of the intervention measured using Perceived Treatment Effect against resource usage (e.g. physiotherapist fees, equipment, medications, etc.), through calculation of the marginal cost effectiveness of treatment in terms of dollars per 1-point improvement in outcome. To accommodate for the possibility of inflated Type I error rate resulting from multiple comparisons, significance will be set at 0.01 (i.e., 99% confidence intervals).

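### Forty per group does not follow from the stated sample-size inputs: an unadjusted two-sided comparison at 0.01 has about 76–78% power and needs 42–44 per group for 80%, a small gap that the planned baseline adjustment probably closes

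*Protocol article*

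**What the plan says.** All inputs come from the protocol article.

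- **Endpoint (Sample size considerations):** "Sample size calculations for this study are based on the 100 mm visual analogue scale for usual pain over the past week".
- **Quantity compared (same section):** "The mean difference between baseline and final score for each group will be compared to measure the effectiveness of each intervention".
- **Effect and spread (same section):** "In order to detect a minimal clinically important difference of 15 mm", "assuming a standard deviation of 20 mm". The text does not say whether the 20 mm is the SD of a single score or of a change.
- **Result (same section):** "a power of 0.80 and alpha level of 0.01, a sample size of 40 participants per group will be required". For dropouts, "a group size of 44 will be recruited, with a total sample size of 176".
- **Significance level (Planned statistical analysis):** "significance will be set at 0.01 (i.e., 99% confidence intervals".
- **Model (same section):** an analysis of variance at each follow-up, "where the baseline value of the outcome measure will be used as a covariate and group allocation as a fixed factor". Randomised participants are included where they have data at the visit, so each loss reduces the number analysed at that visit.

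**The concern.** The sample-size section gives the difference, SD, power, alpha and resulting n together, so the result can be checked directly. The sidedness comes from the analysis section: a 99% confidence interval corresponds to a two-sided test at 0.01. The printed 40 is a little too small for 80% power on those terms.

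Two things depend on it. The first is the accuracy of the power statement. The second is the dropout margin. Going from 40 to 44 implies that 4 per group can be lost over 52 weeks with the stated power kept. If 42 to 44 must be analysed, most or all of that margin is already used.

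**Working it through.** **Inputs.** Difference 15 mm, SD 20 mm, so d = 15/20 = 0.75. Alpha 0.01 two-sided, power 0.80, equal groups.

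**1. Trying to reproduce 40 (normal formula).**

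n = 2(z₀.₉₉₅ + z₀.₈₀)² / d² = 2(2.576 + 0.842)² / 0.75² = 41.5, so 42 per group.

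Power at 40: d√(n/2) = 0.75 × √20 = 3.354, and Φ(3.354 − 2.576) = 78.2%.

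**2. Using t reference distributions**, as an analysis of variance does (noncentral t, noncentrality 0.75√(n/2)):

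| Analysed per group | Normal | Contrast, pooled four-group df (4n − 4) | Two-sample t (2n − 2 df) |
|---|---|---|---|
| 40 | 78.2% | 77.1% | 76.0% |
| 42 | 80.5% | 79.6% | 78.6% |
| 43 | 81.6% | 80.7% | 79.8% |
| 44 | 82.7% | 81.8% | 80.9% |
| **Needed for 80%** | **42** | **43** | **44** |

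**3. Other routes to 40.**

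- One-sided 0.01 gives 2(2.326 + 0.842)² / 0.75² = 35.7, so 36 (normal), or 38 (t). The printed 40 lies between the one-sided and two-sided answers.
- A two-sided alpha of 0.0125 would give 39.6, so 40, but both sections say 0.01.
- An overall four-group F test with a 15 mm range of means needs from 29 to 57 per group, depending on the pattern of means. The article states no pattern.

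**4. Dropout margin.** The implied allowance is 44 − 40 = 4 per group, or 4/44 = 9.1%. With 42, 43 or 44 needed, the margin is 2 (4.5%), 1 (2.3%) or 0. Keeping 9.1% on the unadjusted calculation would take 42/(1 − 0.091), so 47, up to 44/(1 − 0.091), so 49 per group.

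**5. With baseline as covariate, as planned.** Let r be the baseline–final correlation, with equal variances at the two times. The article gives no r, so every value here is an assumption. With the pooled error term, 40 per group reaches 80% once the residual SD is about 19.4 mm or less.

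- *If 20 mm is the SD of the final score*, the residual SD is 20√(1 − r²). At r = 0.25 this is 19.4 mm, so 80% is reached from about r = 0.25 upwards. With the two-group t degrees of freedom the threshold is about 0.28.
- *If 20 mm is the SD of the change*, the residual SD is 20√((1 + r)/2). At r = 0.87 this is 19.3 mm, so 80% holds up to about r = 0.87.
- At r = 0.5 both readings give 20√0.75 = 17.3 mm. About 32 per group are then enough, and 40 per group gives about 89%.

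**The case against.** The strongest reply is that the gap is trivial and belongs to an analysis the trial will not run. By the most common formula, 40 is 2 participants and 1.8 percentage points away from target. The article names no formula or software. The planned model adjusts for baseline, and at an assumed correlation of 0.5 it gives about 87% power with 37 analysed per group (15% lost from 44) and 84% with 35 (20% lost). Sizing on an unadjusted comparison and then analysing with a covariate is common practice and not a contradiction. A condensed article may also leave the dropout rate and the type of SD to the full protocol.

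Most of this stands, and it limits the consequence. It does not make the printed sentence correct. The sample-size section does not invoke the covariate and gives no correlation, so the adjustment cannot be the source of the 40. On the t and F distributions that an analysis of variance uses, the unadjusted shortfall is about 3 to 4 points.

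A reader might go further and infer that the trial will not have 80% power, or that the dropout allowance is worthless. The documents do not support that: both conclusions hold only for the unadjusted comparison, or if baseline adjustment gains very little. A reader might also treat 20 mm as the SD of a single score, apply it to raw change scores, and obtain much lower power at low correlations. The planned model does not analyse raw change scores, so those figures do not describe this trial.

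**Conclusion.** The point holds as a small arithmetic error in the stated sample size. For an unadjusted two-sided comparison at 0.01, with a 15 mm difference and an SD of 20 mm, 40 per group gives about 76–78% power, and 80% needs 42 to 44. On the same basis the 44 recruited allow 0 to 2 losses per group and not 4. This rests on the stated inputs and on reading the 99% confidence intervals as a two-sided test.

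It does not show that the trial is underpowered. Under the planned baseline-adjusted analysis, 40 per group probably reaches 80%, subject to the assumed correlation (at least about 0.25 if 20 mm is a final-score SD, at most about 0.87 if it is a change-score SD). The absence of a dropout rate from a condensed article is not counted as a fault.

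**What to change.** Change the Sample size considerations text in one of two ways:

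1. Keep the unadjusted comparison, say that it is two-sided at 0.01, and state that 40 analysed per group gives about 76–78% power, with 42 to 44 needed for 80% depending on the method; or
2. Base the calculation on the planned baseline-adjusted analysis, saying whether 20 mm is the SD of the final score or of the change, and giving the baseline–final correlation that supports 80% at 40 per group.

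The second is preferable because it matches the planned model and, if the stated correlation is defensible, supports the existing 40 and the existing margin to 44. Either costs a few sentences and at most one added assumption. Enrolment, significance level and analysis stay as they are.

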### Planned statistical analysis

Statistical analysis will be conducted on a blinded, intention to treat basis, with all participants who were initially randomised into the study included where data is available for each measurement time. SPSS software (Version 15.0) will be used for statistical procedures. The four groups will be examined for baseline comparability with respect to demographic data such as age, gender, body mass index and duration of knee pain, as well as baseline values of outcome measures. Continuous outcome measures taken at 6, 12 and 52 weeks will be analysed using univariate analysis of variance, where the baseline value of the outcome measure will be used as a covariate and group allocation as a fixed factor. Continuous data will also be expressed as area under the curve in order to compare the overall effectiveness of each intervention over the entire 12 month period. Participant demographics will also be included in the models as covariates to assess their impact on outcome. The dichotomous measure of success will be analysed using relative risk, risk reduction and numbers needed to treat in order to facilitate clinical interpretation of findings and future guidelines. Cost effectiveness analysis will evaluate the effectiveness of the intervention measured using Perceived Treatment Effect against resource usage (e.g. physiotherapist fees, equipment, medications, etc.), through calculation of the marginal cost effectiveness of treatment in terms of dollars per 1-point improvement in outcome. To accommodate for the possibility of inflated Type I error rate resulting from multiple comparisons, significance will be set at 0.01 (i.e., 99% confidence intervals).

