Foot orthoses are a commonly used and frequently recommended intervention in the management of PFP [7]. Preliminary evidence of their clinical efficacy is provided by findings of a pilot study of 20 adolescent females [8]. The addition of soft foot orthoses to an exercise program resulted in significantly greater improvements in pain than treatment with flat insoles and exercises over eight weeks. A more recent study by Wiener-Ogilvie & Jones [9] however found no difference in outcome between 8 weeks of treatment with functional foot orthoses, exercises, or orthoses with exercises. The authors considered the small sample size (N = 31) to have contributed to the inability to detect a significant difference between the three groups. Conversely, a popular physiotherapy program used routinely in Australia does have high quality RCT evidence to support its use in PFP. Crossley et al [10] showed this six week physiotherapy program of quadriceps muscle retraining, patellofemoral joint mobilisation, patellar taping and daily home exercises to be significantly superior to sham ultrasound, non-therapeutic gel application and placebo taping. The short follow up period used in all three studies could be considered to be a downfall, particularly given the condition's demonstrated tendency for chronicity [3].

In order to provide clinicians with high quality evidence upon which to base clinical decision making, it is therefore timely to conduct a RCT to establish the long term clinical efficacy of foot orthoses in the management of PFP.

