## Discussion

In order to determine the clinical efficacy and cost-effectiveness of foot orthoses in the management of PFP, a pragmatic randomised clinical trial is to be conducted. Based on the Delphi List of criteria for quality assessment of RCTs [29], particular methodological factors have been incorporated into the study design to minimise bias and optimise the rigor of the RCT. Firstly, participants will be randomly allocated to intervention groups via concealed allocation. Poor allocation concealment has been shown to be associated with bias in RCTs [30]. Secondly, the investigator responsible for assessment of outcome at each time point will remain blind to participants' group allocation. Although it could be argued that the use of self-reported primary outcome measures may itself reduce bias associated with an unblinded assessor, blinding of outcome assessors is still an important component due to the potential for transfer of attitudes regarding an intervention from the assessor to the participant [31]. In this study, blinding of participants and the physiotherapists administering treatment is not possible due to the nature of the interventions used. However, as it has been recommended that greater credence should be placed in results where at least the investigators have been blinded to group allocation [31], the single-blind nature of this study is not deemed to be a methodological flaw. Thirdly, the investigators responsible for statistical analysis will be blind to the treatment group allocation, thereby minimising the likelihood of bias associated with their anticipated outcomes. Fourthly, the data analysis will proceed on an intention-to-treat basis, which amongst other things, maintains randomisation, conservatively manages inflation of type I error rate and imitates real life in which it is somewhat likely that not all patients will receive the ideal or intended treatment that has been prescribed.

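### The intention-to-treat label covers an available-case analysis: participants lost by 52 weeks leave the long-term comparison, and their 6- and 12-week values are not used for it

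*Protocol article*

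**What the plan says.** All places are in the protocol article.

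- **Planned statistical analysis, label and inclusion rule.** "Statistical analysis will be conducted on a blinded, intention to treat basis", and, continuing the same sentence, "with all participants who were initially randomised into the study included where data is available for each measurement time".
- **Planned statistical analysis, model.** "Continuous outcome measures taken at 6, 12 and 52 weeks will be analysed using univariate analysis of variance", with the baseline value of the outcome as covariate and group as fixed factor. In addition, "Continuous data will also be expressed as area under the curve in order to compare the overall effectiveness of each intervention". No rule is given for an incomplete curve.
- **Sample size considerations.** Forty per group are required and 44 are recruited. The reason given is "To account for dropouts, particularly considering the long duration of the study".
- **Background.** The stated reason for the trial is "to conduct a RCT to establish the long term clinical efficacy of foot orthoses in the management of PFP".
- **Discussion.** "the data analysis will proceed on an intention-to-treat basis, which amongst other things, maintains randomisation, conservatively manages inflation of type I error rate".

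The only sensitivity analysis named concerns the cut-point for success on the Perceived Treatment Effect scale (Outcome measures).

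**The concern.** The inclusion rule and the model together fix how missing outcomes are handled. A participant seen at 6 and 12 weeks but not at 52 contributes nothing to the 52-week comparison, although two post-randomisation measurements of the same outcome are in hand. The groups compared at 52 weeks are then the attenders within each randomised group.

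This matters most at 52 weeks, the time point for which the trial is run and the one at which the plan itself expects loss. The Discussion says that participants and physiotherapists cannot be blinded, and the arms differ in treatment burden, so reasons for leaving that differ by arm are plausible. If leaving depends on pain after baseline, and does so differently in two arms, the contrast is biased. The extra four participants per group protect power and do nothing about bias.

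This is not detail left to an unseen analysis plan. The protocol article states the rule, the model and the benefit claimed for them.

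**Working it through.** **1. The plan's own figures.** Inputs from Sample size considerations: difference 15 mm, SD 20 mm, power 0.80, alpha 0.01 (taken as two-sided because 99% confidence intervals are planned).

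n per group = 2 × [20 × (2.576 + 0.842) / 15]² = 41.5, so 42. The plan states 40, which is close enough for this purpose. The implied loss is 1 − 40/44 = 9.1%, about 4 of 44 per group or 16 of 176 overall. The plan states no rate of its own.

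**2. What the rule does.** The words on data availability can mean data at the visit being analysed or data at every visit. Under either meaning, a person without a 52-week value is out of the 52-week ANCOVA. Under the second, that person is out at 6 and 12 weeks too. That there is one ANCOVA per visit is inferred from the univariate model with a baseline covariate; it is the natural reading.

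**3. Simple size of the bias.** Let d be the fraction lost in an arm and g the gap in mean 52-week pain between leavers and stayers in that arm. The bias in the contrast is d₁g₁ − d₂g₂. With equal loss it is d × (g₁ − g₂). The gaps, and any loss above 9.1%, are assumptions.

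| Loss | Gaps differ by 10 mm | Gaps differ by 20 mm |
|---|---|---|
| 9.1% (implied) | 0.9 mm | 1.8 mm |
| 20% (assumed) | 2.0 mm | 4.0 mm |

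**4. Simulation with no true difference.** 4,000 two-arm trials, 44 per arm, SD 20 mm, assumed correlations of 0.3 to 0.6 between visits. Dropout before 52 weeks is logistic in the 12-week score (slope 1.2 per SD). The test is two-sided at 0.01.

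| Dropout mechanism | Loss | Bias, available-case ANCOVA | Rejection at nominal 1% |
|---|---|---|---|
| Opposite directions in the two arms | about 18% | about 3.5 mm | 3.5 to 3.8% |
| Opposite directions in the two arms | 9 to 10% | 1.9 to 2.0 mm | about 1.5% |
| Pain-driven in one arm only | 9.1% | about 1 mm | close to 1% |
| Same mechanism in both arms | 9.1% or 18% | within 0.1 mm of zero | about 1% |

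An estimate that fills in the missing 52-week values from baseline and the 12-week value, standing in here for the mixed model, had a bias of 0.1 mm or less throughout. Its standard error matched that of the available-case ANCOVA (about 4.5 mm at 18% loss).

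**5. Simulation with a true 15 mm difference.** SD 20 mm; assumed correlations 0.6 between weeks 12 and 52 and 0.4 with baseline.

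- Worse pain leaves in both arms (14% and 7% lost): the ANCOVA gives 14.3 mm, a shortfall of 0.7 mm.
- Pain drives loss in the control arm only (17% and 5% lost): 13.5 mm, a shortfall of 1.5 mm.
- The worse leave control and the better leave active (14% each): 12.5 mm, a shortfall of 2.5 mm.

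Using the 12-week values gave 14.9 to 15.0 mm in all three.

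**The case against.** The case on the other side has substance.

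- **The rule respects allocation in an important sense.** The Discussion explains intention to treat through patients who do not receive the treatment intended. Those who stop treatment but attend are analysed in their randomised group. That stands, and it is why the wording needs qualifying and not deleting.
- **ANCOVA is not biased by every kind of dropout.** A reader might infer that any link between pain and leaving spoils it. It does not. Baseline pain is in the model, so dropout that depends on group and baseline is harmless, and dropout that works alike in both arms leaves the null contrast unbiased.
- **At the planned loss the effect is modest.** A reader might take 3.5 mm as the expected bias. It needs about twice the implied loss, with opposite mechanisms in the two arms. Nothing in the document predicts either.
- **The control is not an obvious dummy.** It is tempting to say that participants would leave because the insert looks inactive. The section on flat inserts says that it initially looks the same as the orthoses, and the eligibility criteria exclude prior orthosis users to help conceal the difference. Differential dropout remains possible because participants are not blinded overall, but this route to it is unsupported.
- **The area under the curve.** Compounding 9.1% over three visits would suggest that about a quarter of participants lose their curve. The allowance reads as cumulative loss over the study, and no rule for incomplete curves is stated, so that figure cannot be drawn from the document.

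None of this gives a reason to set aside the 6- and 12-week values of people lost at 52 weeks.

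**Conclusion.** The point holds in a limited form. The analysis as written is available-case under an intention-to-treat label. Its 52-week contrast is open to bias if pain-related dropout after baseline differs between arms. The size is about 1 to 2 mm at the implied 9% loss, that is 1/15 to 2/15 of the target difference, or 7 to 13%. It reaches about 3.5 mm in the adverse case. These figures rest on an SD of 20 mm, which the plan gives, and on correlations and dropout mechanisms, which are assumed.

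The Discussion's statements that the approach keeps randomisation intact and handles type I error conservatively are not assured for participants with missing outcomes. In the simulations the rejection rate at nominal 1% stayed at or below about 1.5% near the planned loss, and rose to 3.5 to 3.8% in the adverse case. The documents do not show that the trial will be materially biased. They show that an avoidable risk is left open at the time point that matters most. The change should be made, but the design does not depend on it.

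**What to change.** 1. **Primary model for continuous outcomes.** Replace the per-visit ANCOVAs with one likelihood-based linear mixed model (SPSS MIXED, within the software already named) on all observed 6-, 12- and 52-week values. Fixed effects: group, visit, group × visit, baseline and baseline × visit. Use an unstructured within-person covariance. The baseline × visit term lets the baseline slope differ by visit, as the separate ANCOVAs did.
2. **Estimates.** Read the 6-, 12- and 52-week contrasts from this model. Read the area under the curve from it too, as a time-weighted average of the visit contrasts, so that an incomplete curve needs no separate rule.
3. **Sensitivity analysis.** Add one analysis for data not missing at random, for example with missing 52-week values set 5 to 15 mm worse than predicted, in one arm at a time. Include participants with no follow-up at all, whom the mixed model omits. For scale, a 15 mm shift in one arm at 9.1% loss moves the contrast by 0.091 × 15 = 1.4 mm.
4. **Wording.** In the Discussion, say that participants are analysed in their randomised groups whatever treatment they received. Say also that validity with missing outcomes, including control of type I error, rests on the missing-data assumption and is examined in the sensitivity analysis.

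The cost is slightly more programming and a few sentences of text. No extra participants, visits or data are needed. No material gain in precision should be expected; the benefit is less bias.

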## Methods

### Aim

The primary aim of this study is to determine the clinical efficacy of foot orthoses in the management of PFP, as compared to a flat insole, a proven physiotherapy program, and a combined intervention of foot orthoses and physiotherapy. The cost-effectiveness of foot orthoses compared to the other interventions will also be evaluated.

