#### 4. Foot orthoses and Physiotherapy

Participants assigned to this group will receive both the foot orthoses and physiotherapy programs as described in 1 and 3 above. Due to the large volume of treatment delivered, participants in this group may undergo a seventh visit with the physiotherapist to ensure adequate fit and comfort of the orthoses and understanding and progression of the physiotherapy exercise program.

All participants will receive an educational package at the commencement of the study, providing general information on PFP and advice on activity. In general terms, the advice on activity will entail an encouragement to participants to continue to exercise and participate in activities that do not provoke their knee pain, and to avoid aggravating activities particularly if the provoked pain persists longer than several minutes after cessation of the activity.

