#### 4. Patient Perceived Treatment Effect Score and Perceived Global Effect Visual Analogue Scale

Participants' perceived level of recovery will be rated on two scales at the 6, 12 and 52 week follow-up visits. Perceived Treatment Effect will be measured using a 5 point Likert scale with the following categories: (1) marked worsening, (2) moderate worsening, (3) same, (4) moderate improvement, and (5) marked improvement. For the purpose of analysis, this scale will then be dichotomised according to success, where 'success' is defined as marked or moderate improvement on this scale [10]. We will also conduct a sensitivity analysis on this dichotomisation. Perceived Global Effect Visual Analogue Scale will be piloted. Participants will rate their recovery by placing a vertical mark on a 200 mm VAS with 'same' in the middle to represent no change (0 mm), 'much worse' at the far left end (-100 mm) and 'completely better' as the right hand anchor (+100 mm). A positive score will represent improvement, while a negative score will indicate worsening of the condition.

Secondary outcome measures that will be taken include the following:

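### A dollars-per-point ratio is the only cost-effectiveness result named; on its own it is unreliable and open to misreading for orthoses against physiotherapy or combined treatment

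*Protocol article*

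**What the plan says.** The Aim includes an economic question: "The cost-effectiveness of foot orthoses compared to the other interventions will also be evaluated". The other interventions are the flat insert, physiotherapy, and orthoses with physiotherapy, so two of the three comparisons are with treatments that contain active physiotherapy.

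Planned statistical analysis fixes the method: "Cost effectiveness analysis will evaluate the effectiveness of the intervention measured using Perceived Treatment Effect against resource usage", and the result is to be obtained "through calculation of the marginal cost effectiveness of treatment in terms of dollars per 1-point improvement in outcome". No second economic summary is named.

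The effect measure is described among the primary outcomes: "Perceived Treatment Effect will be measured using a 5 point Likert scale with the following categories". One point is therefore one category. For efficacy, the article says "this scale will then be dichotomised according to success, where 'success' is defined as marked or moderate improvement on this scale".

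The only interval level given is general: "significance will be set at 0.01 (i.e., 99% confidence intervals". Sample size considerations plans 40 analysed and 44 recruited per group.

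**The concern.** The stated statistic divides a difference in cost by a difference in effect. Such a ratio behaves well only when the denominator is clearly away from zero and its sign is known. The article itself makes a small denominator foreseeable: its Background cites an earlier study of 31 patients that found no difference between orthoses, exercises, and the two together.

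The combined arm shows how the sign can cause trouble. Of that arm the article says: "Participants assigned to this group will receive both the foot orthoses and physiotherapy programs as described in 1 and 3 above", so more treatment is delivered there than with orthoses alone. If that makes it dearer overall, and if physiotherapy adds any benefit, orthoses against combined has a negative cost difference and a negative effect difference. The result labelled as dollars per point of improvement would then be dollars saved per point lost.

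At stake is a stated aim of the trial, which could be reported as a number that does not show which treatment is better value and that may have no finite interval.

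**Working it through.** **Inputs from the article.** Usual pain: difference 15 mm, SD 20 mm, power 0.80, alpha 0.01, 40 per group (44 recruited). Level for intervals: 99%, taken as two-sided, z = 2.576. The SD of Perceived Treatment Effect and all costs are not given, so the values used for them below are assumptions.

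**The plan's own sample size.** n = 2 × [20 × (2.576 + 0.842) / 15]² = 41.5, so 42 per group by the normal approximation, close to the stated 40. It matters here only as the source of n.

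**Sign.** This needs no assumption about variability. Take illustrative differences of $200 and 0.4 points, and value a point at an illustrative $1,000. Net benefit = value × effect difference − cost difference.

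| Cost difference | Effect difference | Ratio | Net benefit |
|---|---|---|---|
| +$200 | +0.4 | +$500 | +$200 |
| −$200 | −0.4 | +$500 | −$200 |
| +$200 | −0.4 | −$500 | −$600 |
| −$200 | +0.4 | −$500 | +$600 |

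Each ratio value covers two opposite conclusions; net benefit separates them.

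**When the interval is bounded.** Fieller's interval for the ratio is bounded only if |effect difference| > z × SD × √(2/n). Costs do not enter this condition. It is the same as requiring the effect difference to be significant at 0.01.

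- n = 44: 2.576 × √(2/44) = 0.55 SD.
- n = 40: 2.576 × √(2/40) = 0.58 SD.
- Assumed SD 0.9: 0.49 (n = 44) to 0.52 (n = 40) category.
- Assumed SD 0.5 to 1.2: 0.27 (SD 0.5, n = 44) to 0.69 (SD 1.2, n = 40) category.
- At 95% instead of 99%, SD 0.9: 0.38 to 0.39 category.

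**Chance of a bounded 99% interval** (SD 0.9, n = 40):

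| True effect difference (categories) | 0 | 0.2 | 0.3 | 0.5 | 0.75 | 1.0 |
|---|---|---|---|---|---|---|
| Chance | 1% | 6% | 14% | 46% | 88% | 99% |

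Without assuming an SD: if the standardised difference on this scale equalled the 15/20 = 0.75 SD used for the sample size, the chance would be that test's power, 78% at 40 per arm and 83% at 44.

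**What an unbounded interval looks like.** Assume a cost difference of $200 with standard error $60, no correlation between cost and effect, SD 0.9 and n = 40. With an observed effect difference of 0.7, the 99% limits are about $60 to $1,205 per point. With 0.3, the ratio is $200 / 0.3 = $667, and the 99% set is everything above about $115 together with everything below about −$786. Net benefit for the same data at $500 per point is 500 × 0.3 − 200 = −$50, with 99% interval −$50 ± $302, that is −$352 to +$252.

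**The case against.** Much can be said on the other side.

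- **A reader might infer that the active comparisons cannot be answered.** The article does not support that. A ratio requires both differences to be calculated, nothing says they will be withheld, and a true difference of 0.75 to 1 category would usually give a usable ratio.
- **A reader might infer that orthoses must be cheaper than combined treatment.** That holds for treatment delivered, not for total cost. All groups are planned six visits, the seventh in the combined arm is optional, and costs include medications. Analgesia use and other treatment sought are recorded, so savings in later care could narrow or reverse the gap.
- **A reader might blame the ratio for the chance of an effect estimate with the wrong sign.** That is imprecision at this sample size, and net benefit shares it. With assumed true differences of 0.1 point and $100, effect SD 0.9, cost SD $200 and 44 per arm, net benefit has the wrong sign in about 32% of trials at $500 per point and 40% at $2,000.
- **The article is condensed.** An interval method, a cost-effectiveness plane and rules for dominance may sit in a fuller plan, and their absence is not the point. Nor does the article tie the 99% level expressly to this ratio.
- **The reference arm is not fixed.** Stating combined against orthoses as extra dollars per extra point would resolve that example. But the helpful direction depends on which arm proves better, so it would be chosen after seeing the results.

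What remains is an objection to the statistic that the article does choose. No interval method restores the lost sign or makes a denominator near zero well behaved.

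**Conclusion.** The concern holds in a limited form. As the only named economic result, dollars per point is a poor choice for orthoses against physiotherapy and against combined treatment. The sign ambiguity is a matter of arithmetic and rests on no assumption. The interval threshold of 0.55 to 0.58 SD rests only on the two-sided 99% level and 44 to 40 per arm. Its translation into about half a category rests on an assumed SD of 0.9, with 0.27 to 0.69 over SD 0.5 to 1.2. The dollar figures are illustrations only.

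This should be corrected before analysis, while the presentation cannot be influenced by where the results fall. It does not invalidate the economic aim or the data collected for it.

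**What to change.** For each comparison in the Aim:

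1. Report the cost difference and the effect difference separately, each with a 99% interval, and state which arm is dearer and which is better.
2. Add incremental net benefit (value per unit of effect × effect difference − cost difference) from participant-level data, over a stated range of dollar values, with bootstrap intervals. The unit may be a category or a success.
3. Quote the ratio only where the effect difference is clearly non-zero, with its direction stated.

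This changes the analysis wording only; the same outcome, treatment-log and diary data are used. It gives a finite interval and one meaning for the sign, but leaves the imprecision as it is. The small downside is that results must be shown over a range of values, since the article gives no accepted dollar value per point.
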